Implementing studies that allow more than one new treatment to be tested simultaneously may be advantageous over classic parallel group studies. The main objectives of this type of clinical trial are to quickly reject any new therapies that do not seem to be better than controls and to identify those that are significantly better in terms of clinical outcomes.^(7)^ Thus, we propose a randomized, placebo (PbO)-controlled, adaptive, multiarm, multistage Phase II trial to evaluate ATV, DCV and DCV plus SOF simultaneously to first identify whether any of these drugs alone or in combination reduce the viral load. If they do, a Phase III trial will be initiated to investigate clinical outcomes.

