#### Phase III

The third stage of the study will proceed in a 2:1 allocation (two active treatments for each PbO), with a minimum inclusion of 189 patients and a maximum of 564. The study will perform interim analyses that may interrupt the study due to safety, futility, or efficacy, using all participants already randomized in Phases II/1 and II/2, since the primary efficacy outcome of Phase III (time of use of ventilatory support within 15 days) will be analyzed for all patients from these earlier phases as well.

The hypothesis test for the treatment effect will be performed using a generalized additive model of location and scale considering the distribution of a beta-binomial mixture with inflated zeros for the data adjusted by age and considering the random effect of the center for each intercept (model for the beta-binomial part and for the probability of zeros).

Phase III has three interim analyses planned, m = 3, for each third of the collected sample. The interim analyses consider stop limits according to the O’Brien-Fleming criterion, with significance levels of 0.06%, 1.51% and 4.71%, respectively, to maintain the global significance level at 5%. In Phase III, discontinuations due to futility will be allowed and use the same stopping criteria defined for efficacy.

Although the PbO group is composed of individuals receiving PbOs for three separate drugs (sometimes in combination), it will always be evaluated as a single group after gathering information from all “PbO arms”.

Secondary/exploratory outcomes and additional analyses are described in Supplementary material 1 (Section S4.1).

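### The Phase III futility rule borrows the efficacy levels; read symmetrically it is a harm boundary and would almost never stop an ineffective drug

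*Protocol article*

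**What the plan says.** All the relevant text is in the protocol article, in the Phase III part of the section on primary outcome analysis.

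- Purpose and data: Phase III will have "interim analyses that may interrupt the study due to safety, futility, or efficacy, using all participants already randomized in Phases II/1 and II/2".
- Timing: "Phase III has three interim analyses planned, m = 3, for each third of the collected sample". The third look is in effect the final analysis.
- Efficacy boundary: limits of O'Brien-Fleming type, given as "significance levels of 0.06%, 1.51% and 4.71%, respectively, to maintain the global significance level at 5" percent.
- Futility: "In Phase III, discontinuations due to futility will be allowed and use the same stopping criteria defined for efficacy".
- Size: 2:1 allocation, "with a minimum inclusion of 189 patients and a maximum of 564".

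The futility sentence gives no direction, no conditional or predictive power threshold and no reference effect. The Background describes one aim of trials of this type as to "quickly reject any new therapies that do not seem to be better than controls", and the Discussion calls rapid abandonment of harmful or ineffective approaches equally important.

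**The concern.** An efficacy boundary asks for strong evidence that drug and placebo differ. A futility boundary asks whether the data have made a positive final result unlikely. The two need different thresholds. A drug with no effect gives a test statistic near zero, and a rule that needs an extreme statistic will not react to it.

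A drug that does nothing clinically can plausibly reach Phase III. Phase II selects on viral load decay with a global type I error of 0.20 in its first stage, and the Discussion concedes that the link between viral load and clinical outcome is debated. If the futility provision does not work, such a drug takes the trial to full size, and the DSMB has a rule that is called futility but detects harm.

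**Working it through.** **Inputs from the article.** Three looks at thirds; nominal levels 0.0006, 0.0151 and 0.0471; Phase III adds 376 active and 188 placebo patients; final totals are 314 placebo and 439 to 502 active.

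**Assumptions.** The levels are two-sided: the article does not say so, but two-sided z-values give the O'Brien-Fleming shape (step 1). Power is not given, so 80% and 90% are used. The final-look drift is θ = 1.985 + 0.842 = 2.827 or 1.985 + 1.282 = 3.267. Information is taken as proportional to 1/(1/n_active + 1/n_placebo).

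**1. The stated boundary.** The levels convert to z = 3.432, 2.430 and 1.985. Multiplied by √t at t = 1/3, 2/3 and 1 they give 1.981, 1.984 and 1.985, which is nearly constant, as O'Brien-Fleming requires. The overall two-sided error is 5.24% at equal thirds and 5.02% to 5.05% with Phase II patients pooled, against the stated 5%. That small difference is a separate matter and does not affect this point.

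**2. Pooled information fractions.** Phase II contributes 439 − 376 = 63 active (or 502 − 376 = 126) and 314 − 188 = 126 placebo patients. With 63 active:

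- look 1: 188.3 active, 188.7 placebo, information 94.25
- look 2: 313.7 active, 251.3 placebo, information 139.5
- final: 439 active, 314 placebo, information 183.1

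The fractions are 0.515, 0.762 and 1. With 126 active they are 0.558, 0.780 and 1.

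**3. Symmetric reading: stop if Z₁ ≤ −3.432 or Z₂ ≤ −2.430, drug with no effect.**

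- Look 1: Φ(−3.432) = 0.03%.
- Look 2, not already stopped: 0.74%.
- Total: 0.77% at equal thirds and 0.76% at both sets of pooled fractions.

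An early efficacy stop by chance is equally likely at equal thirds, so about 1 − 2 × 0.0077 = 98.5% of null trials reach the final look, apart from safety stops.

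On the effect scale, stopping needs an estimate of −c/(θ√t) times the design effect. At 90% power and equal thirds this is −3.432/(3.267 × 0.577) = −1.82 at look 1 and −2.430/(3.267 × 0.816) = −0.91 at look 2. The drug must look about as harmful as it was hoped to be beneficial, or more so. Even a drug whose true harm is half the size of the design effect is stopped only 10% to 14% of the time (80% to 90% power, equal thirds).

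**4. A dedicated futility rule for comparison.** With B = Z√t, conditional power under the planned effect is Φ((B + θ(1 − t) − 1.985)/√(1 − t)). It is below 20% when B < 1.985 − θ(1 − t) − 0.842√(1 − t). At 90% power and equal thirds:

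- look 1: B < 1.985 − 2.178 − 0.687 = −0.880, so Z < −1.52
- look 2: B < 1.985 − 1.089 − 0.486 = 0.410, so Z < 0.50

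Simulation (4 million paths per scenario) gives:

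| Assumed power | Looks at | Null trials stopped by look 2 | Power lost (points) |
|---|---|---|---|
| 80% | equal thirds | 75% | 0.6 |
| 90% | equal thirds | 69% | 0.2 |
| 80% | 0.515, 0.762 | 85% | 0.8 |
| 90% | 0.515, 0.762 | 82% | 0.3 |

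The symmetric rule stops 0.8% in every row.

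**The case against.** **The same levels can make a workable futility rule.** If they are used to reject the design alternative (stop if Zₖ − θ√tₖ ≤ −cₖ), null trials stop 45% (80% power) or 59% (90%) of the time at equal thirds, and 52% or 66% at fractions 0.515 and 0.762. A drug with the design effect is stopped 0.8% of the time. The planned effect would normally be found in the SAP, to which the article sends the sample size details and further statistical methods, and the SAP was not available for this review. This objection stands in part: a sound rule may have been intended. But it tests a different hypothesis and needs a reference effect, and the sentence states neither. The article also does not simply leave futility to the SAP; it states a rule.

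**A stronger reading does not hold.** A reader might infer that the trial stops for futility whenever the efficacy level is not met. At look 1 that would drop a drug with the full design effect 94% to 96% of the time at equal thirds, or 86% to 92% at fraction 0.515 (90% to 80% power). The document does not support this: every trial would then end at look 1, which contradicts three planned looks and a maximum of 564. The plan should not be charged with discarding effective drugs.

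**The consequences are limited.** The Background sentence describes trials of this type in general, and the main early rejection is the Phase II gate, which ends the study if no arm beats placebo. Phase III can also stop for safety. A missing futility stop does not inflate type I error, bias the estimate or reduce power. All of this stands and lowers the severity. It does not make the stated futility provision work.

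**Conclusion.** Wrong as written; should be fixed. Read symmetrically, which is its natural sense, the sentence defines a harm boundary under the name of futility. It would stop a drug with no effect before the final look about 0.8% of the time, so a null Phase III would nearly always recruit all 564 patients. The 0.8% rests on two-sided levels and does not depend on assumed power; it is the same with or without pooled Phase II data. The comparison figures for other rules do depend on the assumed 80% to 90% power. The cost is wasted patients and time, not an invalid Phase III conclusion.

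**What to change.** Replace the sentence with a separate futility rule that states its direction, its reference effect and that it is non-binding. One example: the DSMB may recommend stopping if conditional power under the planned effect is below 20% at look 1 or look 2. Conditional power is one option among several; whichever is chosen, its operating characteristics should be given for the planned effect and the actual information fractions. If a test against the design alternative was intended, say so and give the effect. Keep the lower mirror boundary, but call it a harm boundary.

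The cost is wording in the protocol, SAP and DSMB charter, plus about 0.2 to 0.8 percentage points of power for the example rule. Because the rule is non-binding, the efficacy levels stay as they are. The change should be settled before any unblinded Phase III look.

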#### Interim analyses

One interim analysis is planned in Phase II (first stage), 1 in Phase II (second stage) and 3 in Phase III, and 3 interim analyses will be conducted, as described in detail in the statistical methods section.

The database will be blocked after obtaining a 15day follow-up for all patients, and all necessary actions to obtain follow-up data will be performed. All interim analyses would be made available to *Agência Nacional de Vigilância Sanitária* (Anvisa).

### Ethical aspects and good clinical practices

#### Ethical considerations and dissemination

The trial was designed according to the guidelines for good clinical practice, follows the principles of the Declaration of Helsinki, and was approved by the *Comissão Nacional de Ética em Pesquisa* (Conep; n° 4.799.171, June 23, 2021), Anvisa (n° 107/2020) and the Ethics Committee (EC) guidelines at each center.

Patients are included after the signed Informed Consent Form is obtained by the investigators participating in the study. In addition, all eventual amendments to the protocol must be approved by the REC/Conep system before its implementation by the participating centers.

The study will be submitted for publication after completion, regardless of its findings. Manuscript preparation will be an inalienable responsibility of the Steering Committee. The main paper will be authored by the Steering Committee members plus the principal investigators of the ten top recruiting sites, who will contribute intellectually to the manuscript.

### Adverse events

All adverse events will be recorded by the investigators on the clinical records (CRF), regardless of severity, and graded according to the Division of AIDS (DAIDS) Severity table. Table 1S (Supplementary material 1) shows the known adverse events resulting from the use of the products under investigation and explains the main actions to implement for SAEs.

The principal investigator at the research center is responsible for informing research ethics committees of any SAEs within 24 hours, as required by local regulations, except those that are classified as study outcomes.

The HCor Research Institute is responsible for receiving and monitoring all adverse events that occur during the clinical study. All adverse events classified as serious according to the definition of RDC Anvisa 09/15 must be informed to the sponsors within a maximum period of 24 hours of knowledge through a specific email. After evaluation, Fiocruz and Blanver Farmoquímica e Farmacêutica must notify Anvisa of serious, unexpected reports whose causality is possible, probable or defined in relation to the product under investigation within the regulatory deadlines.

### Study organization

#### Protocol violations and deviations

Major deviations related to the inclusion or exclusion criteria, study conduction, and patient management must be reported to the coordinating site.

#### Trial organization and oversight

The Steering Committee comprises the study investigators and is responsible for the development of the study protocol, manuscript drafts and study submission for publication. A team from the HCor Research Institute coordinates the study in association with the Brazilian Research in Intensive Care Network (BRICNet) and Coalition Brazil. The HCor Research Institute has been responsible for conducting the study since its inception and managing and controlling data quality. The Data Safety and Monitoring Board (DSMB) is composed of an external statistician and 2 other researchers who are experts in critical care medicine. The DSMB is responsible for the interim analysis and for providing guidance to the Steering Committee regarding the continuation and safety of the trial after the interim analyses.

#### Current status

We randomized 256 patients from April until July 2021. The first DSMB meeting occurred in May and June 2021. After analyzing data according to DSMB Charter, the DSMB recommended continuing the trial as planned.

### Dissemination policy

The results of the study will be disseminated in presentations at congresses and submitted for publication in high impact scientific journals.

## DISCUSSION

This manuscript describes the protocol of the REVOLUTIOn trial, which is a randomized, PbO-controlled, adaptive, multiarm, multistage study to evaluate the efficacy of ATV, DCV and SOF simultaneously compared with their PbOs. The main objective is to identify whether any of these drugs alone or in combination are capable of reducing viral load and, if so, investigate the clinical outcome of increasing the number of days free of respiratory support in a larger population.

Expeditious and methodologically rigid clinical trials are demanding to identify safe and effective treatments. Nevertheless, rapid identification and abandonment of harmful or ineffective approaches are equally important, especially during a pandemic. The principal aim of the REVOLUTIOn trial is to aid in the recognition of any of these 3 repurposed antivirals as treatments for COVID-19. The multiarm, multistage design of REVOLUTIOn helps rapidly identify the effectiveness of these drugs in a seamless manner and at the same time, starting with a Phase II clinical trial focusing on safety and ending with a Phase III trial capable of answering clinically important questions.

Repurposed drugs are important in resource-limited settings because the interventions are more rapidly available, have already been tested safely in other populations and are inexpensive.

Limitations of the protocol are described below. First, decisions related to changing stages rely on a decreasing viral load in the initial phases despite extensive debate on the association of viral load with worse clinical outcomes.^(12)^ Second, late initiation in recruiting participants in the pandemic timeline slowed our recruitment rate, as pandemic cases steadily decreased after vaccination outset and, third, late protocol publication, although the content of this protocol paper is absolutely consistent with the protocol submitted and approved by the national/local Ethics Research Committee, our national regulatory agency (Anvisa) and ClinicalTrials.gov.

## CONCLUSION

In conclusion, the REVOLUTIOn study protocol explains the design and purpose of the study, which has the objective of answering whether repurposed antiviral drugs are effective and safe treatments for COVID-19 in an adaptive, multiarm, multistage design starting with a Phase II clinical trial and ending with a Phase III trial.

## Figures and Tables

**Table t6:** Summary of versions

Version	Date
v4.0	Feb 26th / 2021
v3.0	Dec 28th / 2020
v2.0	Oct 30th / 2020
v2.0	Oct 15th / 2020
v1.0	Sep 09th / 2020
v1.0 August 2020	Aug 07th / 2020
Original project v1.0 July 2020	Jul 27th / 2020
